## Abstract

**Background:**

Overweight and obesity pose a global public health challenge and have a multifactorial origin. One of these factors includes obesogenic environments, which promote ultraprocessed foods characterized by being high in calories, saturated fats, added sugars, and sodium. In Mexico, it has been estimated that 30% of the total energy consumed comes from processed foods. The Modification to the Official Mexican Standards introduces nutritional information through black octagonal seals that alert consumers about products with excessive amounts of some components for a better food selection in the population. However, the effects of warning labels on processed food selection and purchases among children remain unknown.

**Objective:**

We aimed to evaluate the impact of a digital educational intervention focusing on front-of-package warning labels on the food selection and purchasing behavior of elementary schoolchildren and their caregivers.

**Methods:**

Children from 4 elementary schools in Mexico City, 2 public and 2 private schools, will participate in a randomized controlled trial. The schools will be chosen by simple random sampling. Schools will be randomized into 2 groups: intervention and control. In the control group, the dyads (caregiver-schoolchildren) will receive general nutritional education, and in the intervention group, they will receive guidance on reading labels and raising awareness about the impact of consuming ultraprocessed products on health. The educational intervention will be conducted via a website. Baseline measurements will be taken for both groups at 3 and 6 months. All participants will have access to an online store through the website, allowing them to engage in exercises for selecting and purchasing food and beverages. In addition, other measures will include a brief 5-question exam to evaluate theoretical understanding, a 24-hour reminder, a survey on food habits and consumption, application of a food preference scale, anthropometric measurements, and recording of school lunch choices.

**Results:**

Registration and funding were authorized in 2022, and we will begin data collection in September 2024. Recruitment has not yet taken place, but the status of data analysis and expected results will be published in April 2025.

**Conclusions:**

The study is expected to contribute to evaluating whether reinforcing front-of-package warning labels with education enhances its effects and makes them more sustainable. Conducting this study will allow us to propose whether or not it is necessary to develop new intervention strategies related to front-of-package labeling for a better understanding of the population, improved food choices, and better health outcomes.

**Trial Registration:**

ClinicalTrials.gov NCT06102473; https://clinicaltrials.gov/study/NCT06102473

**International Registered Report Identifier (IRRID):**

PRR1-10.2196/54783

## Introduction

Overweight and obesity pose a global public health challenge. In Mexico, data from the National Health and Nutrition Surveys from 2012, 2018, and 2020 show that the combined prevalence of overweight and obesity in children between the ages of 5 and 10 years has remained high (33.2%, 35.6%, and 38.2%, respectively) [1].

Obesity has a multifactorial etiology, involving genetic, environmental, and behavioral aspects. Obesogenic environments promote ultraprocessed foods, which are high in calories, saturated fats, added sugars, and sodium [2,3].

Therefore, public policies aimed at reducing the incidence and prevalence of childhood obesity must consider actions that modify the environment to improve nutrition. Labeling of ultraprocessed products has been a common strategy that governments worldwide use to improve people’s diets [4].

In Mexico, it has been estimated that more than 30% of the total energy consumed comes from ultraprocessed foods, favoring the prevalence of overweight and obesity. The daily dietary guidelines by the Ministry of Economy and the Ministry of Health in Mexico were an effort for people to improve their food selection and purchasing; however, they did not show good results due to the complexity of interpreting them [5].

The Modification to the Official Mexican Standard (NOM-051-SCFI/SSA1-2010 [NOM 051]) was approved in 2020. This proposed a front labeling system for foods and beverages that consisted of nutritional information through black octagonal seals, with legends like “excess calories,” “excess sodium,” “excess saturated fat,” “excess trans fat,” “excess sugars,” and other explanations, such as “contains caffeine, avoid for children” and “contains sweeteners, not recommended for children,” to provide information to the consumers to help them make food selections [5,6].

Ultraprocessed products targeted at children are offered in all supermarkets and represent an important commercial income for the food industry [7,8]. At home, parents are primarily responsible for purchasing food and have a significant influence on their children’s eating behaviors [7-10].

On the other hand, children also influence parents’ purchasing decisions, especially when they want to choose unhealthy foods, which is why the influence of front labeling must be studied from both perspectives (ie, children’s and parents’) [11]. To reduce the purchase and consumption of ultraprocessed foods, various marketing strategies have been implemented, especially for products aimed at school children; however, the results have been varied and limited [12,13].

It is known that food packaging has an impact on how children perceive these products. For instance, the use of drawings and bright colors can make them associate the product with something suitable to eat, which is why changes have been made to packaging designs to discourage consumption, mainly by removing cartoon slogans or legends that promote their consumption [14].

Some types of front-of-package labeling guide the daily intake by indicating the proportion (%) of nutrients found in a serving according to the recommended daily intake for adults. This includes the traffic light system, which uses colors (green, yellow, and red) to indicate the amount of nutrients in a product, as well as warning labels, which are black octagonal symbols, which indicate the excess of nutrients, energy, and substances present in the product and are intended to discourage purchase and consumption [15].

Having identified the relationship between packaging and food consumption, it is expected that front-of-package nutritional labels will reduce the consumption of unhealthy foods [16].

Furthermore, it has been documented that another effective strategy to improve food selection is to enhance nutritional education to develop skills to distinguish healthy products from those that are not considered healthy [17].

Mobile nutritional interventions have been observed to reach a broader range of social and demographic groups and can facilitate the selection of healthy foods at the point of purchase, optimizing decision-making times [18].

In Mexico, it is estimated that 78.6% of the Mexican population aged 6 years and older has access to the internet, with 97% connecting through mobile devices. This is why various health institutions have implemented web portals, social networks, and the use of cell phone messages, telephone, and mobile apps for managing, preventing, and treating health-related activities [19-21].

The objective of this clinical trial is to evaluate the impact of a digital educational intervention focusing on front-of-package warning labels on the food selection and purchasing behavior of elementary school children and their caregivers [22].

## Methods

### Recruitment and Study Design

Third-, fourth-, and fifth-grade elementary school students and their caregivers from 4 primary schools—2 public and 2 private schools—in Mexico City will participate in the study. The schools will be chosen by simple random sampling. Schools will be randomized into 2 groups: intervention and control.

After approval from the directors of the primary schools, meetings will be held with parents to invite them to participate; they will be explained the intervention’s objectives, activities, and duration. Parents and schoolchildren will be invited to sign a consent and informed assent, respectively, clarifying that their participation is voluntary, and they may choose to discontinue at any time without affecting their activities at school.

The main question this study aims to answer is the following: What is the effect of a digital educational intervention about front-of-package warning labels on food selection among children attending primary schools in Mexico City, compared to a control group?

Schools will be randomized into 2 groups. In the control group, the dyads (caregiver-schoolchildren), will receive general nutritional education, and in the intervention group, they will also receive guidance on reading labels, which raises awareness about the impact of consuming processed or ultraprocessed foods on health.

The intervention will be carried out via a website [23] (Figure 1) with audiovisual material, and all participants will also be asked to complete a multiple-choice evaluation (5 questions) to ensure a theoretical understanding of the topics. Other measures will include a lunch register, 24-hour dietary recall, a survey of food habits and consumption, a validated food preference questionnaire, anthropometric measurements (eg, weight, height, and waist circumference), a socioeconomic survey, as well as participation in a simulated web-based food and beverage selection and shopping activity. These measures will help assess if the digital educational intervention on front-of-package warning labeling for children and caregivers improves the selection and purchase of foods.

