### Statistical Analysis

Descriptive statistics will be used to characterize variables, and tables will be made with summary measures. Independent *t* tests and chi-square tests for categorical data will be used to compare baseline characteristics between the intervention and control groups. The Mann-Whitney *U* test will be used to evaluate differences between groups in case of nonnormal distribution.

Repeated measures ANOVA will be used to evaluate the change in the number of warning labels in nutrient consumption between groups and throughout the intervention. We will use a mixed-effects model to evaluate the effect of the intervention on changes in food and beverage selection, adjusting for confounding variables. Intention-to-treat analysis will be performed.

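### No restriction of the school randomisation by public or private type is stated; if there is none and each arm gets two schools, there is a 1-in-3 chance that arm and school type coincide

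*Protocol article*

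**What the plan says.** The composition of the sample is fixed. The abstract (Methods) says "Children from 4 elementary schools in Mexico City, 2 public and 2 private schools, will participate in a randomized controlled trial", and Recruitment and Study Design repeats that pupils and caregivers "from 4 primary schools—2 public and 2 private schools—in Mexico City will participate in the study".

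For selection and allocation, the same section says "The schools will be chosen by simple random sampling. Schools will be randomized into 2 groups: intervention and control", and it repeats the allocation statement later in the section. The abstract describes both steps in the same way. None of these places mentions stratifying, pairing or otherwise restricting either step by school type, and none gives the number of schools per arm.

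On adjustment, Statistical Analysis says "We will use a mixed-effects model to evaluate the effect of the intervention on changes in food and beverage selection, adjusting for confounding variables". The confounders are not named, so school type is neither included nor excluded.

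**The concern.** The fixed split of two and two shows that the authors regard school type as a feature worth balancing in the sample. Neither described step uses it. A simple random sample of schools, taken literally, does not guarantee two of each type, so selection must in practice be done within type. Nothing comparable is said that would keep the types balanced between arms.

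With only four units to randomise, imbalance on a two-level factor is not a remote event. If both public schools fall in one arm, the comparison of intervention with control is also a comparison of public with private schools. It is reasonable to assume, though the article gives no figures, that the two types differ in family resources, purchasing habits and engagement with a website programme. All of these bear on food selection in the online shop. The article's main question, the effect on food selection compared with a control group, would then be mixed with the effect of school type.

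**Working it through.** The article gives no probability, sample size or power figure on this point, so there is no stated figure to reproduce.

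**Inputs**
- Four schools, two public and two private (abstract, Methods; Recruitment and Study Design).
- The school is the unit of randomisation, with no restriction by type stated (same places).
- Allocation ratio: not stated. Two readings are worked through: exactly two schools per arm, and an independent fair coin toss per school. Randomisation within type is the comparison.

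**Reading 1: unrestricted, two schools per arm**
- Number of allocations: C(4,2) = 6.
- Allocations in which arm equals type: the intervention arm is either both public or both private schools, so 2.
- Probability: 2/6 = 33.3%.

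**Reading 2: independent coin toss per school**
- Number of outcomes: 2^4 = 16.
- Arm equals type: 2/16 = 12.5%. Given that both arms have at least one school, it is 2/14 = 14.3%.
- One arm empty: 2/16 = 12.5%.
- Together: 4/16 = 25% of draws give either no comparison or one that cannot be separated from school type.
- A further 8/16 = 50% split the schools 3:1, leaving one arm with a single school.

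**Comparison: randomisation within type**
- Number of allocations: 2 × 2 = 4, each with one public and one private school per arm.
- Arm equals type: 0 of 4.

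**Can adjustment separate the two effects?** Take the school-level design matrix with columns for intercept, arm and school type, with the two public schools listed first.
- Arm = (1, 1, 0, 0), type = (1, 1, 0, 0): the two columns are identical and the rank is 2 of 3. Arm and type are fully aliased, and adding more children per school does not change this.
- Arm = (1, 0, 1, 0), type = (1, 1, 0, 0): the rank is 3 of 3, so both terms can be estimated.

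**What randomising within type costs and leaves**
- Allocations fall from 6 to 4, so the smallest possible two-sided randomisation p-value rises from 2/6 = 0.33 to 2/4 = 0.50. Neither could support a conclusion at a conventional level.
- With intercept, arm and type fitted to four schools, 4 − 3 = 1 residual degree of freedom remains at school level.

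**The case against.** The strongest objection is that the article is silent rather than explicit. It does not say that school type is ignored. It condenses a fuller protocol that is not shown, and the fixed split of two and two is compatible with one school of each type per arm. A reader might infer that the schools are definitely randomised without regard to type; the text does not support that. This part of the objection stands, and it makes the point conditional. It does not remove the point. The article names a selection method and a unit of allocation, and followed as written they permit a fully confounded comparison.

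Second, the 1-in-3 figure depends on two schools per arm, which is nowhere stated. This also stands. Depending on the procedure, the chance of full aliasing is 0% (within type), 12.5% (coin tosses) or 33% (unrestricted 2:2).

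Third, simple random sampling combined with a fixed number of each type can be read as simple random sampling within each type. That is fair. The wording is loose, and reading it as a contradiction that changes the trial goes too far.

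Fourth, a reader might conclude that an aliased draw would leave no interpretable answer at all. The design softens this:
- Dyads without internet access or devices are excluded in both arms (Exclusion Criteria).
- A socioeconomic survey is taken at baseline, and food selection is measured at baseline, 3 months and 6 months (Primary Outcomes, Time Frame).
- The model targets change in selection, so stable differences in level between school types are largely removed.

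These features help with household-level differences, and only where those overlap between the types. They do not address different trends over time, different engagement with the website, or other school-level differences tied to type.

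**Conclusion.** The point holds in conditional form. The article states no restriction of the school randomisation by type. If there is none and each arm receives two schools, the chance that arm and school type coincide is 2/6 = 33%. With independent coin tosses it is 12.5%, plus 12.5% for an empty arm. In an aliased draw the planned adjustment cannot include school type alongside arm, and the other design features reduce the harm only in part.

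The result rests on two assumptions: that no unpublished restriction by type exists, and that public and private schools differ in ways that affect change in food selection. The matter is worth settling before the draw, because the damage cannot be undone once the schools have been allocated. Randomising within type removes this one failure; having only two schools per arm remains a serious limit of the design either way.

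**What to change.** Replace the selection and allocation sentences in the abstract and in Recruitment and Study Design with wording to this effect: two public and two private schools will be drawn at random from the eligible schools of each type; within each type, one school will be randomised to intervention and the other to control. In Statistical Analysis, name school type as a stratum in the mixed-effects model.

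If the full protocol already randomises within type, the article need only say so.

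The cost is a few changed sentences and one restricted draw. The article reports that recruitment has not begun and that work in schools is expected to start in September 2024, so the change is possible if the schools have not yet been allocated. The statistical price is the fall from 6 to 4 possible allocations and one school-level degree of freedom for the stratum. The text should also acknowledge that two schools per arm leaves differences between individual schools mixed with the intervention effect, which stratifying does not cure.

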**Figure 1 figure1:**
[figure not shown]
Website “Applicate por tu salud” (www.viviendo-saludable.org).

### Inclusion Criteria

Inclusion criteria for children are as follows: students in third, fourth, and fifth grades (aged 8 to 12 years), of both sexes, enrolled in the selected primary schools, with normal weight, overweight, and obesity, who sign the written informed consent.

Inclusion criteria for caregivers are as follows: primary caregivers of any sex of children in the third, fourth, and fifth grades with normal weight, overweight and obesity, who sign the written informed consent.

### Exclusion Criteria

Caregivers and children without internet access, computers, or mobile devices, as well as those participating in a weight reduction program with pharmacological treatment, will be excluded.

### Nutritional Education Interventions

The control group and the intervention group in dyads (caregiver-schoolchildren) will receive general nutritional education, and only the intervention group will receive guidance on reading warning labels, which raises awareness about the impact of consuming processed and ultraprocessed foods on health.

On the website, there will be 4 sections. Participants will receive an account and password to access the educational content corresponding to the group they belong, intervention or control group.

The intervention and control groups will have access to the first section, which contains general nutritional education topics. The second section will contain nutritional education topics related to warning labeling, and only the intervention group will have access to it.

Each topic will be presented through videos, released every 15 days, as well as weekly infographics and tips to the caregivers and children via the website. This material will also be sent to the participants’ mobile devices.

The third section will have the “Online shop,” which will be used as part of the food selection evaluation. The fourth section will evaluate theoretical understanding with 5 multiple-choice questions per topic (Figure 2).

**Figure 2 figure2:**
[figure not shown]
Nutritional intervention topics by groups.

### Primary Outcomes

#### Time Frame

The measurements will be carried out in 2 scenarios (in schools and through the website) at baseline (1 week before starting the educational interventions), at 3 months, and at 6 months after the intervention ends.

A socioeconomic survey will be used in the baseline measurement.

The following assessments will be conducted at 3 frame times (baseline, 3 months, and 6 months): a food preference questionnaire, a 24-hour dietary recall, lunch register, and a survey of food habits and consumption. Anthropometric measurements (eg, weight, height, and waist circumference) will only be performed at baseline and the end of the 6-month intervention.

Through the website, dyads will engage in food and beverage purchasing exercises in the online shop simulator at the 3 measurement points (baseline, 3 months, and 6 months), along with multiple-choice evaluation (5 questions).

#### Food and Drink Selection

The percentage of products purchased by each participant in the online store, whose content indicates “high in calories, sugar, fat, and sodium” and the average content of these nutrients in 100 g of each product will be measured.

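### The per-100 g nutrient average, one of two measures of the primary selection outcome, can improve when a sugary drink is added to the basket and so conflict with the other measure

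*Protocol article*

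**What the plan says.** In the Protocol article, Primary Outcomes, the subsection Food and Drink Selection gives two measures in one sentence. The first is a share: "The percentage of products purchased by each participant in the online store" that are marked "high in calories, sugar, fat, and sodium". The second is the nutrient average: "the average content of these nutrients in 100 g of each product will be measured". No weight for quantity or pack size is given for either.

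Foods and drinks are handled together throughout. The Abstract (Methods) describes one online store, "allowing them to engage in exercises for selecting and purchasing food and beverages". Time Frame says that "dyads will engage in food and beverage purchasing exercises in the online shop simulator at the 3 measurement points". Statistical Analysis treats the two as one domain: "We will use a mixed-effects model to evaluate the effect of the intervention on changes in food and beverage selection". The article mentions no separate beverage measure and no per-100 mL basis.

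**The concern.** Drinks are mostly water, so even a sugary one usually has less energy, fat and sodium per 100 g than a typical solid product. In an average that counts each product once, a drink pulls the mean down, however large the bottle and however much sugar it adds to the basket.

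Sugary drinks are an obvious target of education on warning labels. If intervention dyads drop them, the nutrient average can rise and read as harm. If control dyads add them, it can fall and read as benefit. The percentage measure would normally move the other way. The trial could then report two measures of one primary outcome that disagree in direction, for a reason that has nothing to do with the quality of the foods chosen.

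**Working it through.** The article states no figure to reproduce. The direction follows from algebra alone; the sizes need product values, which the article does not give and which are assumed here.

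**Direction.** Take a basket of n products with mean content m per 100 g, and add one product with content d.

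- New mean minus old mean = (nm + d)/(n + 1) − m = (d − m)/(n + 1). This is negative whenever d < m. Removing such a product raises the mean.
- If k of the n products are 'high in' and the added drink is too, the share goes from k/n to (k + 1)/(n + 1). This is a rise whenever k < n, and no change if k = n.

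So for a 'high in' drink with d < m, the two measures move in opposite directions unless every product in the basket is already 'high in'.

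**Six-item basket (assumed values).** Per 100 g: kcal, g sugar, g saturated fat, mg sodium; then pack weight.

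- Biscuits: 450, 25, 8, 350; 170 g; 'high in'
- Cereal: 380, 30, 1, 400; 300 g; 'high in'
- Yogurt: 90, 12, 1.5, 50; 500 g; 'high in'
- Bread: 265, 5, 0.8, 450; 600 g
- Apples: 52, 10, 0, 1; 800 g
- Beans: 110, 0.5, 0.1, 5; 500 g
- Added drink: 42, 10.5, 0, 10; 600 g; 'high in'

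| | Before | After adding the drink | Reads as |
|---|---|---|---|
| Mean energy, kcal/100 g | 1347/6 = 224.5 | 1389/7 = 198.4 (−12%) | better |
| Mean sugar, g/100 g | 82.5/6 = 13.8 | 93/7 = 13.3 (−3%) | better |
| Mean saturated fat, g/100 g | 11.4/6 = 1.9 | 11.4/7 = 1.6 (−14%) | better |
| Mean sodium, mg/100 g | 1256/6 = 209.3 | 1266/7 = 180.9 (−14%) | better |
| Share 'high in' | 3/6 = 50.0% | 4/7 = 57.1% | worse |
| Total energy, kcal | 4911 | 4911 + 6 × 42 = 5163 | worse |
| Total sugar, g | 305 | 305 + 6 × 10.5 = 368 | worse |
| Total sodium, mg | 4778 | 4778 + 6 × 10 = 4838 | worse |
| Total saturated fat, g | 29.4 | 29.4 | unchanged |

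**Two-item basket (assumed values).** A 100 g pack of cookies at 450 kcal and 30 g sugar per 100 g, plus a 600 mL drink (taken as 600 g) at 42 kcal and 10 g sugar per 100 g. Mean energy goes from 450 to (450 + 42)/2 = 246 kcal/100 g (−45%), and mean sugar from 30 to 20 g/100 g (−33%). Energy bought rises from 450 to 450 + 252 = 702 kcal, and sugar bought from 30 to 90 g.

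**Range for a ten-item basket, change = (d − m)/11.**

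- Energy, drink at 20 to 60 kcal: the mean falls in every case with m from 100 to 400 kcal/100 g, by 3.6 to 34.5. At m = 50, a 60 kcal drink raises it by 0.9.
- Sugar, drink at 10.5 g: +0.50 at m = 5, +0.23 at m = 8, −0.14 at m = 12, −1.32 at m = 25. The reversal for sugar is conditional.

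**Would weighting by grams cure it?** No. In the six-item basket (2870 g, then 3470 g), the pooled gram-weighted energy goes from 4911/28.7 = 171.1 to 5163/34.7 = 148.8 kcal/100 g, and sugar stays at 10.6 g/100 g. Splitting does cure the mixing: the food average stays at 224.5 kcal/100 g, and the drink appears in the beverage average at 42.

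**The case against.** A reader might infer that the primary selection outcome as a whole has the wrong sign, or that it mainly tracks the drink-to-food mix. The document does not support either. The percentage measure stands beside the nutrient average and normally counts an added 'high in' drink as worse. How much the average depends on the mix turns on the shop's catalogue and task rules, which the article does not give. If the exercise fixes the number of items per category, the drink share cannot shift and the reversal disappears.

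Nor should the 45% fall be read as typical: it needs a basket of one solid product and one drink. A group-level figure has a similar limit. With foods at 350 and drinks at 35 kcal/100 g (assumed), cutting drinks from 30% to 15% of items moves the mean from 255.5 to 302.75 (+18%), but only if the foods chosen do not change at all.

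Three more points deserve a fair hearing.

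- *Pooling is an inference, and a condensed article may leave scoring to the full protocol.* This stands in part: the article does not say outright that one mean covers foods and drinks. It is the natural reading of one outcome, one shop and one model. The fault also does not hang on the silence about quantity, since a pooled gram-weighted mean falls too.
- *Content per 100 g is a fair measure of product choice.* It is for swaps: replacing a sugary drink with water lowers the mean, which is the right sign. It misleads when the number of drink items changes.
- *Amounts are covered by the outcome Energy and Macronutrient Intake.* That outcome measures what is consumed, not what is selected in the shop, so it does not correct the selection measure.

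**Conclusion.** The concern holds for the nutrient-average measure of Food and Drink Selection, on the reading that foods and drinks are averaged together. That measure can improve when a sugary drink is added and worsen when one is dropped: usually for energy, fat and sodium, and for sugar only when the basket mean exceeds the drink's value. Since the percentage measure and the basket totals of energy and sugar move the other way, two parts of one primary outcome can conflict.

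The direction rule needs no product data. The sizes do: about 12% for energy in the six-item basket and 45% in the two-item basket, all on assumed contents, with fat taken as saturated fat and the added drink assumed to be 'high in'. The article gives no basis for saying how often baskets would differ in this way.

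**What to change.** Change the definition under Food and Drink Selection as follows.

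1. Keep the percentage of 'high in' products as the lead selection measure.
2. Compute the nutrient average separately for foods (per 100 g) and for beverages (per 100 mL or per 100 g).
3. Report basket totals of energy, sugar, saturated fat and sodium alongside it. Do not divide these totals by grams: that gives a density again, which shows no change when two identical drinks become one.

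The cost is more figures per nutrient, computed from the same shop records with no new visit. The beverage average is undefined for a basket without drinks, so the number of such baskets should be reported, and this is one reason to have the totals. The totals need the net content of every product in the simulator, which the article does not confirm is recorded. If it is not, the split into foods and beverages alone still removes the mixing error.
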